**Methods/Design:**

In this multicenter, randomized, controlled superiority trial, 542 patients scheduled for elective, high-risk abdominal surgery will be included. Patients are allocated to standard care (control group) or early goal-directed therapy (intervention group) using a randomization procedure stratified by center and type of surgery. In the control group, standard perioperative hemodynamic monitoring is applied. In the intervention group, early goal-directed therapy is added to standard care, based on continuous monitoring of cardiac output with arterial waveform analysis. A treatment algorithm is used as guidance for fluid and inotropic therapy to maintain cardiac output above a preset, age-dependent target value. The primary outcome measure is a combined endpoint of major complications in the first 30 days after the operation, including mortality. Secondary endpoints are length of stay in the hospital, length of stay in the intensive care or post-anesthesia care unit, the number of minor complications, quality of life, cost-effectiveness and one-year mortality and morbidity.

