### Statistical analysis and sample size calculation

A study of the hospital data of one of the participating centers revealed that the number of major complications embedded in the composite primary endpoint was 0.58 per patient, and that a Poisson distribution was applicable. We aim to reduce the number of major complications per patient by 30% (from 0.58 to 0.41). Using Poisson regression with an assumed two-sided error of 5%, we calculated that a sample size of 226 patients in each group will be needed to detect this reduction with a power of 80%. For the multicenter character of the study, a 20% correction was made, since the variance between the participating centers is unknown. This results in a total sample size of 542, or 271 patients in each group.

Statistical analysis will be performed using SPSS version 21.0 for Windows (SPSS Inc, Chicago, Illinois, United States). The first analysis will be performed by combining the results from the participating centers. After this, the results of the individual centers are analyzed to detect possible differences. The primary analysis consists of a comparison of the primary endpoint (number of complications per patient) between the control group and the EGDT group using Poisson regression. According to secondary endpoints, data will be checked for normal distribution and presented as mean +/-standard deviation when normally distributed, and as median +/-interquartile range when not normally distributed. Relative risks are presented with 95% confidence intervals. Categorical data are tested with Fisher’s exact test. Continuous data are tested with the independent samples t-test when normally distributed, and with the Mann-Whitney U test if not normally distributed. A *P* value <0.05 is considered statistically significant. Analysis will be carried out according to the intention-to-treat principle.

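### 226 patients per group give about 73–75% power, not 80%, for the planned Poisson comparison, so the 20% multicenter step to 542 mostly makes up that shortfall

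*Protocol article*

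**What the plan says.** All inputs are in the protocol article under Statistical analysis and sample size calculation.

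- Control rate, from hospital data of one participating center: "the number of major complications embedded in the composite primary endpoint was 0.58 per patient", with the further finding "that a Poisson distribution was applicable".
- Effect: a 30% reduction, printed as 0.58 to 0.41.
- Test: "Using Poisson regression with an assumed two-sided error of 5" percent.
- Base size: "we calculated that a sample size of 226 patients in each group will be needed to detect this reduction with a power of 80" percent.
- Inflation: "For the multicenter character of the study, a 20% correction was made, since the variance between the participating centers is unknown". This takes the total to 542, or 271 per group.

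The same section names Poisson regression on the number of complications per patient as the primary analysis. Allocation is 1:1 ("Trial design"). The abstract carries the final figure forward: "542 patients scheduled for elective, high-risk abdominal surgery will be included". The sample-size formula is not named.

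**The concern.** The planning inputs and the primary test are both given, so the stated power can be checked directly. The usual two-group Poisson calculations on these inputs return more than 250 patients per group, not 226. If the base is too small, the 20% added for unknown between-center variance does a different job from the one described: it brings the base up to the size it should have had.

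The article itself gives reasons to want that margin. The 0.58 comes from one center. The "Standard care" discussion accepts that routine care may be heterogeneous, and the arterial waveform device varies by hospital. The "Primary endpoint" discussion describes one deteriorating patient contributing three complications, which could push the variance of the counts above the Poisson value. A neutral result would be read as coming from a trial with 80% power and a 20% reserve, when most of that reserve has been used up.

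**Working it through.** **Inputs.** Control rate λ1 = 0.58. Intervention rate λ2 = 0.406 (exactly 30% lower, rate ratio RR = 0.70) or 0.41 (as printed, RR = 0.707). Two-sided 5% (z = 1.960), 80% power (z = 0.8416), 1:1 allocation.

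**1. Reproducing the plan's figure.** The Signorini-type formula for Poisson regression with a binary covariate, with null variance at the control rate in both arms, gives

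N = [1.960·√4 + 0.8416·√(2 + 2/RR)]² / (0.58·ln(RR)²).

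- RR = 0.70: (3.920 + 1.855)² / (0.58 × 0.12722) = 451.96, so 452 in total or 226 per group. This matches.
- RR = 0.41/0.58: 476.98, about 239 per group. This does not match.

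The inflation also reproduces: 226 × 1.2 = 271.2 and 452 × 1.2 = 542.4.

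**2. Why that formula is optimistic here.** Its null term uses a variance of the log rate ratio, times n per group, of 2/0.58 = 3.45. The Wald test uses 1/0.58 + 1/0.406 = 4.19. Even a pooled null at the mean rate of 0.493 gives 2/0.493 = 4.06. Fewer events in the intervention arm mean a larger variance on the log scale, and the formula leaves this out of its null term.

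**3. Size needed per group for 80% power.**

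| Method | λ2 = 0.406 | λ2 = 0.41 |
|---|---|---|
| Wald on log scale: (1.960 + 0.8416)²·(1/λ1 + 1/λ2)/ln(λ2/λ1)² | 258.3 | 271.6 |
| Rate difference: (1.960 + 0.8416)²·(λ1 + λ2)/(λ1 − λ2)² | 255.6 | 268.9 |
| Square-root scale: (1.960 + 0.8416)²/[2(√λ1 − √λ2)²] | 253.6 | 266.9 |
| Log scale with pooled null variance | 252.7 | 266.0 |
| Exact enumeration of the two Poisson totals (score and likelihood ratio; Wald) | 254; 256 | 268; 269 |

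One-sided 5% versions of the four formulas give about 199–214, so a sidedness slip does not explain 226.

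**4. Power at the stated sizes.** The Wald approximation is Φ(|ln(λ2/λ1)|/√[(1/λ1 + 1/λ2)/n] − 1.960). For n = 226 and λ2 = 0.406 this is Φ(0.3567/0.1361 − 1.960) = Φ(0.660) = 74.6%.

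| n per group | λ2 = 0.406: approximation; exact | λ2 = 0.41: approximation; exact |
|---|---|---|
| 226 | 74.6%; 75.1–75.4% | 72.4%; 72.9–73.2% |
| 271 | 81.8%; 82.3–82.5% | 79.9%; 80.4–80.6% |

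The exact ranges span the Wald, score and likelihood-ratio tests.

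**5. Margin left in 271 per group.**

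- λ2 = 0.406: 271/258.3 = 1.05 to 271/254 = 1.07, so about 5–7%.
- λ2 = 0.41: 271/271.6 = 1.00 to 271/268 = 1.01, so about 0–1%.

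**6. If variance really were 20% larger.** The effective size is 271/1.2 = 225.8 per group, and the Wald approximation gives 74.5% (0.406) or 72.4% (0.41).

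**The case against.** Four objections deserve weight.

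*The figure is not an arithmetic slip.* A reader might infer a miscalculation. The documents do not support that: a Poisson-regression planning formula returns 452 exactly at a rate ratio of 0.70, and the multiplication by 1.2 is correct. This stands, with the caveat that the article names no formula, so its use is inferred from the match. What fails is the step from that formula's output to 80% power for the test that will be run.

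*The design input was probably 0.406.* Since 226 reproduces at 0.70 and not at 0.41/0.58, 0.41 looks like a rounded display value. On that reading the shortfall is about 5 points and some 5–7% of margin survives. This also stands. A claim that almost nothing of the allowance is left holds only for the printed 0.41.

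*The trial as sized reaches 80%.* A reader might infer that 542 patients are too few. On the article's stated assumptions they are not: power is about 80–82%. The article attaches 80% to 226 per group and gives no power figure for 542.

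*The 20% is a precaution, not an estimate.* The article calls the between-center variance unknown. Randomization is stratified by hospital in blocks, so differences in baseline rate between centers should largely cancel from the treatment comparison. The 72–75% is therefore a conditional scenario, not the trial's expected power. Nor should the statement that a 20% correction was made be removed, because the correction was made. What needs qualifying is how much of it remains as margin.

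**Conclusion.** The point holds in this form: the stated 80% power at 226 per group is wrong for the planned two-sided Poisson test. The power is about 75% for an exact 30% reduction and about 73% for the printed 0.41, a shortfall of 5 to 7 points. Nothing else in the article repairs this. The step from 226 to 271 mostly closes that gap and leaves a margin of about 5–7% or 0–1% for between-center variance, where the text implies 20%.

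These figures rest on the article's own inputs: 0.58 per patient, variance equal to the mean, 1:1 allocation and two-sided 5%. The 72–75% at 542 also assumes variance 20% above Poisson, which the plan allows for but does not estimate. The finding concerns a misstated power and a misdescribed reserve. It does not show that the trial is too small on its stated assumptions.

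**What to change.** In the section Statistical analysis and sample size calculation, keep the account of how 226 and 542 were reached and amend it as follows:

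1. Name the formula used and the intervention rate entered (0.406 or 0.41).
2. State that 226 per group gives about 73–75% power for the planned Poisson regression, and that 80% needs about 254–258 (0.406) or 267–272 (0.41) per group.
3. State that 542 patients give about 80–82% power with pure Poisson counts and no center variance or overdispersion, and that power would be about 72–75% if variance were 20% larger.
4. Say that the 20% correction was applied to an optimistic base, so that little of it remains as a margin for between-center variance.

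The cost is wording only. The stated power becomes less favourable, and recruitment need not change.

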### Randomization

A randomization procedure is used to allocate patients to standard care (control group) or standard care with EGDT (intervention) in a 1:1 ratio. The randomization is stratified according to hospital and type of surgery. In each stratum, a block randomization with variable block size is applied using a computer.

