### Methodological aspects

#### RCT design

Especially in studies evaluating perioperative hemodynamic therapy, randomized controlled trials (RCTs) have a number of limitations, such as impossibility to blind at the patient and caregiver level, and the Hawthorne effect [34, 47, 48]. The Hawthorne effect is a phenomenon whereby clinicians tend to improve care for patients included in studies, which may affect outcome in both the control and intervention groups [49]. We discussed the alternative approach of a before-after study. For the purposes of our study, prospective data collection is necessary. Therefore, the Hawthorne effect will be present in both ‘before’ and ‘after’ periods. More importantly, postoperative outcome after high-risk surgery is multifactorial. It is simply impossible to keep all these factors constant during the entire study period, which was the main reason for choosing the RCT design. Since the start of our trial, a number of important aspects in the care for high-risk surgical patients have changed. First, robotic surgery is increasingly being used in our institutions. Second, surgical safety checklists have been introduced in many centers, reducing both mortality and morbidity after surgery [50]. In one of the participating centers in this trial this led to a significant reduction in 30-day in-hospital mortality [51]. Similar checklists have been implemented in the other participating centers. We therefore regarded randomization to be crucial in this study. We stratified the randomization procedure with respect to participating center and type of surgery, since these covariates may influence outcome to a great extent. The number of patients in certain strata may become small however, which was the reason for applying blocked randomization.

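### The stated primary Poisson comparison names neither stratification factor, and analyzing centers one by one does not test whether the effect differs between them

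*Protocol article*

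**What the plan says.** Protocol article, Randomization: "The randomization is stratified according to hospital and type of surgery". The RCT design section gives the reason, "since these covariates may influence outcome to a great extent", and adds a caution, "The number of patients in certain strata may become small however", which it answers by randomizing in blocks.

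Statistical analysis and sample size calculation: "The first analysis will be performed by combining the results from the participating centers". The primary analysis is a "comparison of the primary endpoint (number of complications per patient) between the control group and the EGDT group using Poisson regression". No covariate, stratum or random effect is named. The next step for centers is: "After this, the results of the individual centers are analyzed to detect possible differences". No treatment-by-center interaction test is mentioned, and type of surgery is given no role in the analysis.

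Three hospitals were recruiting when the article was written and a fourth was expected (Study setting; Trial status).

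**The concern.** When randomization is balanced within strata that predict outcome, the analysis normally carries those strata too. Otherwise the standard error may include variation that the design has already balanced out. Here the article itself calls the factors important and then states a comparison that uses neither.

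The center step raises a different problem. The device used for arterial waveform analysis is chosen by each institution, and standard care follows local routine, so readers will want to know whether the effect varies by center. Fitting each center separately asks whether each small sample shows an effect by itself. It does not ask whether the effects differ. Centers with the same true effect can easily fall on opposite sides of p=0.05.

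**Working it through.** **Inputs from the article.** Control rate: "the number of major complications embedded in the composite primary endpoint was 0.58 per patient". Reduction 30%, so the exact intervention rate is 0.7 × 0.58 = 0.406 (printed as 0.41). Two-sided 5%, power 80%, 226 per group, raised by 20% to 271 per group (542 in total). Three centers, later four.

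**Assumptions.** The article gives no stratum rates and no center sizes. I take equal centers for power per center, and a coefficient of variation (CV) of stratum rates from 0.3 to 0.7.

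**1. The plan's own sample size.** Log rate ratio, with the null variance taken at the control rate:

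n = [1.96·√(2/0.58) + 0.8416·√(1/0.58 + 1/0.406)]² / ln(0.58/0.406)² = (3.640 + 1.722)² / 0.1272 = 225.98, so 226.

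Then 452 × 1.2 = 542.4, so 542. The stated figure is reproduced.

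**2. Primary test, model-based standard error.** Simulation of 3,000 trials per scenario: four centers (weights 0.3, 0.3, 0.2, 0.2) by two types of surgery, balanced allocation within strata, Poisson counts within strata, rate ratio 0.41/0.58 = 0.707 for power.

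| Assumed stratum rates | Type I error, unadjusted / adjusted | Power, unadjusted / adjusted |
|---|---|---|
| 0.31 to 1.03 | 0.046 / 0.046 | 0.810 / 0.815 |
| 0.19 to 1.40 | 0.051 / 0.050 | 0.787 / 0.796 |

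The true log rate ratio is −0.347. The mean unadjusted estimates are −0.350 and −0.341, so there is no material bias. The level holds because balance within strata cancels the between-stratum variation, and the ordinary Poisson variance never counts it.

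**3. Primary test, robust standard error.** A robust variance without strata does count that variation. With m the mean rate in an arm, the variance factor per arm is 1 + m·CV², which adds 2·CV²/271 to the variance of the log rate ratio.

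- Adjusted: SE = √[(1/0.58 + 1/0.406)/271] = √0.01545 = 0.1243. Power = Φ(0.3567/0.1243 − 1.96) = Φ(0.909) = 82%.
- Unadjusted: power = Φ(2.869 − 1.96·R), where R is the ratio of the unadjusted robust SE to 0.1243.

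| CV | Unadjusted SE | R | Power |
|---|---|---|---|
| 0.3 | √(0.01545 + 0.00066) = 0.1269 | 1.02 | 81% |
| 0.5 | √(0.01545 + 0.00185) = 0.1315 | 1.06 | 79% |
| 0.7 | √(0.01545 + 0.00362) = 0.1381 | 1.11 | 76% |

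The simulation agrees in direction and size. For the two scenarios in step 2, robust power is 0.79 unadjusted against 0.82 adjusted, and 0.73 against 0.80. Unadjusted type I error is 0.040 and 0.031, against 0.048 and 0.052 adjusted.

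**4. Separate center analyses.** Power per center = Φ(0.3567/√[(1/0.58 + 1/0.406)/n] − 1.96), with n patients per group in the center.

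- Four centers, n = 271/4 = 67.75: SE 0.2486, power 30%.
- Three centers, n = 271/3 = 90.3: SE 0.2153, power 38%.

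If the effect is the same everywhere and each center is judged by p<0.05:

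- Four centers: all significant 0.30⁴ = 0.8%; none 0.70⁴ = 24%; mixed 1 − 0.008 − 0.24 = 75%.
- Three centers: mixed 1 − 0.38³ − 0.62³ = 71%.

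If there is no effect anywhere, at least one center reaches p<0.05 with probability 1 − 0.95³ = 14% or 1 − 0.95⁴ = 19%.

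**5. What a comparison between centers can show.** With four centers, the difference between two center log rate ratios has SE 0.2486·√2 = 0.352. One center's rate ratio would have to be about exp(1.96 × 0.352) = 2.0 times another's to reach significance. An interaction test answers the right question but has low power.

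**The case against.** The strongest reply is that the article never says the model is unadjusted. Combining centers describes whose data enter, and a center-adjusted model combines centers too. Covariates may be listed in the full protocol or an analysis plan not shown here. This stands as a limit: a reader might infer that the factors are certainly left out, but the text shows only that the stated comparison names two groups and nothing else.

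A second reply is that robust standard errors are not mentioned, so the larger losses in step 3 do not apply to the test as written. This also stands. On the model-based test the cost is about one point of power.

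A reader might further infer a biased treatment effect. Randomization and the collapsibility of the rate ratio rule that out, and blocking within strata limits chance imbalance.

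A reader might also infer that the 20% increase in sample size is wasted because a center term would remove the variance it pays for. The documents do not support this. They do not say which between-center variance is meant, and a center term removes baseline differences but not differences in treatment effect. The extra patients also raise the Wald power for 0.58 against 0.41 from 0.72 at 226 per group to 0.80 at 271.

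Finally, the center sentence prescribes no p-value per center and attaches no decision to one. True, so the 75% applies only if centers are judged by significance. Under any reading, however, separate fits give no test of a difference.

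**Conclusion.** The point holds in a limited form. The stated primary comparison does not carry the factors used in randomization, although the article calls them influential. The consequence is lost precision, not bias. It is about one point of power under the model-based Poisson test, and roughly one to six points if a robust standard error is used and the stratum CV lies between 0.3 and 0.7, a range the documents neither confirm nor exclude.

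The center-by-center step is the firmer part, since it needs no assumption about stratum variation. It rests on equal centers and a common 30% reduction, and it cannot show whether the effect differs between hospitals.

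Adjusting for the strata does not deal with extra-Poisson variation within them. That is a separate question.

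**What to change.** State in the analysis section that the primary Poisson regression includes center and type of surgery as fixed effects, at the levels used in randomization. Replace the separate center analyses by one treatment-by-center interaction test, labelled exploratory and low in power, with each center's rate ratio and 95% confidence interval shown descriptively.

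The change affects wording only and needs no new patients or data. It uses a few degrees of freedom against about 271 × (0.58 + 0.406) = 267 expected complications. Very small strata may have to be pooled. The article does not say how many levels type of surgery has, so the pooling rule should be written down in advance. Because the trial is unblinded, the model should be fixed before outcomes are compared by group.

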## Background

### High-risk surgery

Both the extent of the surgical procedure and the presence of comorbidities increase the risk of an adverse outcome after surgery. Moreover, approximately 12.5% of all surgical patients are considered as ‘high-risk’ [1, 2]. The majority of perioperative complications and death occur in this minority of patients [1]. With increasing age and comorbidities in the general population, the number of high-risk surgical patients is expected to grow. Approximately 50% of these surgical patients develops one or more perioperative complications, and mortality in this specific patient group is around 5% [1–6]. Major complications such as myocardial infarction, cardiac failure, stroke, pneumonia, renal failure, or sepsis, involve a significant burden to the patient and to hospital facilities during the hospitalization period [3]. After discharge, these complications may result in long-term disability, cognitive impairment and even death, significantly reducing quality of life and increasing healthcare consumption [3].

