### Data collection

Before the operation demographic data, ASA physical status, medical history, and drug usage are collected from the patient’s medical records.

A number of hemodynamic variables (blood pressure, HR, CI, and SVV if applicable) are recorded each hour during the first 24 hours after induction. In the EGDT group, these variables are also recorded before and after interventions to correct a drop in CI below the target value. Fluid balance in the first 24 hours is evaluated by recording the amount of fluids infused (crystalloid, colloid, and blood products) as well as urine output and blood loss. In addition, the use of inotropes is registered (type, amount, and duration of infusion). The following laboratory variables are determined after induction, during surgical closure, after admittance to the ICU/PACU, and the morning after surgery: serum hemoglobin, lactate, and full blood gas analysis (arterial and venous). After admittance to the ICU/PACU, the following additional blood values are determined in order to calculate the Sequential Organ Failure Assessment (SOFA) score [32]: serum creatinine, bilirubin, and platelet count. The morning after surgery, serum troponin and creatinine levels are measured. The Therapeutic Intervention Scoring System (TISS) is calculated after admittance to the ICU/PACU [33]. Variables are derived from the patient monitoring systems used in the operating room and ICU/PACU, or from the OR and ICU/PACU record systems.

The following information is obtained in the first 30 days after surgery: all-cause mortality, major and minor complications, if applicable; duration of postoperative mechanical ventilation (hours); length of stay in the in the hospital (days) and ICU/PACU (hours); length of stay in the in the hospital (days) and ICU/PACU (hours) according to fit-for-discharge criteria [5] (Additional file 3); continuation of care at intermediate care units (hours); number of readmissions to the ICU/PACU or intermediate care unit.

All information can be obtained from the patients’ medical records. Patient follow-up with respect to complications and length of stay is active.

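### The primary Poisson comparison is described without ASA status or age; prespecifying both would cost nothing and, if they are prognostic, would improve precision and error control

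*Protocol article*

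**What the plan says.** The section on statistical analysis and sample size calculation defines the primary analysis as a "comparison of the primary endpoint (number of complications per patient) between the control group and the EGDT group using Poisson regression", by intention to treat. It lists no covariate. It also does not call the analysis unadjusted or exclude adjustment.

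The same section bases the sample size on one center's data, in which "the number of major complications embedded in the composite primary endpoint was 0.58 per patient", and adds "that a Poisson distribution was applicable". The target is a 30% reduction to 0.41, with 226 patients per group, raised by 20% to 542 in total.

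On baseline data, the Data collection section says: "Before the operation demographic data, ASA physical status, medical history, and drug usage are collected". On risk, the High-risk surgery section opens with: "Both the extent of the surgical procedure and the presence of comorbidities increase the risk of an adverse outcome after surgery". Under Eligibility criteria, group 1 procedures are open to any ASA status, while group 2 procedures require ASA III or IV. Randomization is stratified by hospital and type of surgery. The RCT design section describes those two factors as potentially strong influences on outcome.

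**The concern.** The trial's idea of high risk rests partly on comorbidity, and ASA status is its recorded measure. It is known before allocation and is not a stratification factor. Within group 1 it can differ between arms by chance. Age is not balanced by design either.

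If patients differ in underlying rate, the count varies more than a Poisson count with one common rate. An arm-only model leaves that extra variation in the treatment comparison. Two things are then at stake:

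- the true precision of the rate ratio, in a design with little spare power;
- the honesty of the ordinary Poisson standard error, which takes variance equal to mean and is too small when rates vary.

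With a log link, and a treatment ratio that is the same across risk levels, the adjusted and unadjusted rate ratios target the same quantity. Adjustment therefore does not change the question.

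**Working it through.** **1. Reproduce the plan's figure.** Inputs from the sample size section: control rate 0.58, 30% reduction (ratio 0.70), two-sided 5%, power 80%, 1:1. Signorini's formula for Poisson regression on a binary covariate:

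N = (1.96·√V0 + 0.8416·√V1)² / (0.58·(ln 0.70)²), with V0 = 4 and V1 = 2 + 2/0.70 = 4.857.

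This gives N = 451.96, so 452 in total or 226 per group, and 452 × 1.2 = 542.4, so 542. The stated size reproduces exactly from arm alone and does not rely on adjustment.

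**2. Margin at 271 per group.** With the rates as printed (0.58, 0.41), the Wald variance of the log rate ratio is (1/0.58 + 1/0.41)/271 = 4.163/271 = 0.01536. Then |ln(0.41/0.58)| = 0.3469 and power = Φ(0.3469/0.1239 − 1.96) = 79.9%. At exactly 30% (0.406) it is 81.8%. Neither figure allows for variance between centers.

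**3. Gain from adjustment.** Let CV² be the squared coefficient of variation of the patient's rate that ASA status and age explain. Then

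Var(unadjusted) = (1/0.58 + 1/0.41 + 2·CV²)/271,

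and adjustment removes the 2·CV² term. I assume half the patients are ASA III-IV, rate ratio R for ASA, rate ratio A per SD of age, and the two independent:

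- CV²(ASA) = 0.25(R − 1)²/(0.5 + 0.5R)²
- CV²(age) = exp((ln A)²) − 1
- CV² = (1 + CV²(ASA))(1 + CV²(age)) − 1

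The last column is the unadjusted type I error with ordinary Poisson errors and 0.58 in both arms: 2[1 − Φ(1.96/√(1 + 0.58·CV²))].

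| R, A (assumed) | CV² | Variance reduction | Power unadjusted, correct SE | Power adjusted | Type I, ordinary SE |
|---|---|---|---|---|---|
| 1.5, 1.15 | 0.061 | 2.8% | 78.8% | 79.9% | 5.4% |
| 1.75, 1.2 | 0.111 | 5.0% | 77.8% | 79.9% | 5.7% |
| 2.0, 1.3 | 0.190 | 8.4% | 76.4% | 79.9% | 6.3% |
| 2.5, 1.4 | 0.326 | 13.5% | 74.0% | 79.9% | 7.2% |

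Example, third row: 2 × 0.190 = 0.381, and 0.381/(4.163 + 0.381) = 8.4%. If CV² = 0, every gain is zero.

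**4. Ordinary Poisson errors.** Simulation with 3,000 trials per setting, 271 per arm, ASA ratio 2 and log-rate SD 0.3 for age (CV² = 0.216):

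- Null rejection was 6.6% unadjusted and 5.1% adjusted.
- Under 0.58 versus 0.41, rejection was 79.3% and 80.5%.
- The mean reported standard error did not shrink (0.1244 and 0.1247). The true spread of the estimate did (0.1302 and 0.1237).
- The mean log ratio was about −0.35 both ways and about 0 under the null.

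**5. Chance imbalance.** Without stratification, the SD of the difference in ASA III-IV share is √(2·0.25/271) = 4.3 points. A 2-SD imbalance is 8.6 points and, at R = 2, shifts the ratio by 1.543/1.457 = 1.059. Stratification by type of surgery reduces this, because ASA is fixed at III-IV for group 2. If 30% of patients are in group 2 (assumed), the group 1 share is 0.2/0.7 = 0.286 and the SD is √(2·0.7·0.286·0.714/271) = 3.2 points. Two SDs are then 6.5 points and the shift is about 4.4%.

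**The case against.** The strongest objection is that silence is not exclusion. This is a condensed article, the full protocol and analysis plan are not shown, and a covariate list is often kept there. A reader might infer that the plan forbids adjustment; the text does not say so. What remains is that the article describes a two-group comparison, and its sample size matches an arm-only model. Naming the covariates is therefore a concrete better method to offer.

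A reader might also infer that the planned result is biased or invalid. It is not. Randomization protects the comparison on average, and a correct standard error already allows for chance imbalance. The shifts of 4 to 6% above are 2-SD events, about 1 in 20, at an assumed ASA ratio of 2.

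A third objection is that the loss of precision is not shown. This stands in part. No effect of ASA or age is given, and the article's statement that a Poisson distribution applied, taken literally, leaves nothing to remove. However, that statement comes from one center, and at CV² = 0.19 the variance-to-mean ratio is only 1 + 0.58 × 0.19 = 1.11, a departure that is easily missed. One rate for all patients also fits poorly with the article's own account of comorbidity.

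The documents do not call age a driver of complications. They link it to growth of the high-risk population and use it to set the cardiac index target. The case for age is weaker than for ASA status.

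Finally, a robust variance alone would repair the type I error. That is correct, but it would leave the lower power where it is.

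**Conclusion.** The point holds as an inexpensive improvement, with modest benefit under plausible assumptions. The true-variance reduction of about 3 to 13% rests on the assumed rate ratios, a 50% share of ASA III-IV, independence of ASA and age, and no other heterogeneity. It is measured against an arm-only model. Against a model that already contains type of surgery it would be smaller, by an amount the documents do not allow one to compute.

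Which benefit appears depends on the standard error. If it is correct, adjustment recovers roughly 1 to 6 points of power. If it is the ordinary Poisson one, power changes by only about 1 to 2 points, and the gain is mainly that type I error returns to about 5%. The documents do not support calling the analysis wrong, biased or self-contradictory on this point.

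**What to change.** Before the data are analyzed, state the primary model in one sentence: Poisson regression on arm, with ASA status (I-II versus III-IV) and age (continuous) as prespecified covariates, together with hospital and type of surgery, and with a robust variance. Report the unadjusted rate ratio as a supporting result. If the unseen analysis plan already says this, nothing further is needed.

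The change needs no new data and no new patients, since ASA status and demographics are already recorded before surgery. It should be fixed before results are seen, because clinicians, patients and observers are all unblinded and covariates chosen later would be less credible.
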